# START – physical exercise and person-centred cognitive skills training as treatment for adult ADHD: protocol for a randomized controlled trial

**DOI:** 10.1186/s12888-023-05181-1

**Published:** 2023-09-25

**Keywords:** ADHD, Cognitive support, Intervention, Physical activity, RCT

## Abstract

**Background:**

Core symptoms in attention deficit hyperactivity disorder (ADHD) are inattention, impulsivity and hyperactivity. Many individuals with this disorder also have a sedentary lifestyle, co-morbid mental illness such as depressive and anxiety disorders, and reduced quality of life. People with ADHD often have impaired executive function, which among other things may include difficulty in time management and structuring of everyday life. Pharmacological treatment is often the first-line option, but non-pharmacological treatment is also available and is used in clinical settings. In children and adolescents with ADHD, physical exercise is used as a non-pharmacological treatment. However, the evidence for the effectiveness of exercise in adults is sparse.

**Objective:**

To implement the START intervention (START = *Stöd i Aktivitet, Rörelse och Träning* [Support in activity, movement and exercise]) consisting of a 12-week, structured mixed exercise programme with or without a cognitive intervention, in adults with ADHD, and study whether it has an effect on core symptoms of ADHD as well as physical, cognitive, mental and everyday functioning compared with usual treatment. A secondary aim is to investigate the participants’ experiences of the intervention and its possible benefits, and to evaluate the cost-effectiveness of START compared with usual treatment.

**Methods:**

This is a randomized controlled trial planned to be conducted in 120 adults with ADHD, aged 18–65. The intervention will be given as an add-on to standard care. Participants will be randomized to three groups. Group 1 will be given a physiotherapist-led mixed exercise programme for 12 weeks. Group 2 will receive the same intervention as group 1 with the addition of occupational therapist-led cognitive skills training. Group 3 will be the control group who will receive standard care only. The primary outcome will be reduction of ADHD symptoms measured using the World Health Organization (WHO) Adult ADHD Self-Report Scale (ASRS-v1.1), Clinical Global Impression-Severity scale (CGI-S) and CGI-Improvement scale (CGI-I). The effect will be measured within 1 week after the end of the intervention and 6 and 12 months later.

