### Sample size estimation

The power calculation is based on the primary outcome, ADHD symptom reduction assessed using the World Health Organization (WHO) Adult ADHD Self-Report Scale (ASRS-v1.1) [32]. Postulating a mean difference in symptom reduction of 15% between the intervention and control groups, with 10.63% SD, 0.05 alpha, 0.8 power and expecting a 25% drop-out, gives a sample size of 120 participants. The actual sample size required for a power of 0.8 is 90 (= 120–120*25%). In case we have larger than 25% drop-out, we will recruit more participants to maintain the necessary power of 0.8.

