### Participants

Recruitment will primarily be conducted by the General Psychiatry outpatient clinic and the clinic for young adults at Örebro University Hospital, Örebro, Sweden. Eligible persons will receive written and oral information about the study and a consent form when visiting the clinic. Participants will also be recruited via the following channels: the 1177 website (the official website for all county-based health care in Sweden); the Örebro County Facebook account; and the National Association of Neurodevelopmental Disorders, Riksförbundet Attention. Interested persons will be invited to contact the research team to receive written and oral information about the study and a consent form. Individuals who agree to participate in the study and are eligible according to the inclusion and exclusion criteria will be included. To assess eligibility for inclusion, their medical history will be retrieved from the medical records.

Inclusion criteria: Diagnosed with ADHD; age 18–65 years; stable medication or no medication.

Exclusion criteria: Ongoing depression (Montgomery-Asberg Depression Rating Scale, Self-Assessment (MADRS-S) score > 21), suicidality, bipolar disorder, psychosis, substance abuse, severe autism, reported threatening behaviour, and severe physical illness, as well as inability to read/understand Swedish.

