**Primary outcome measures (ADHD symptoms)**								
MADRS-S*	PT					P	P	P
WHO Adult ADHD Self-Report Scale (ASRS-v1.1)		P		P		P	P	P
Clinical Global Impression-Severity (CGI-S)	AP					AP	AP	AP
Clinical Global Impression- Improvement (CGI-I)						AP	AP	AP

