### Primary outcome measures

Changes in ADHD symptoms:

The WHO Adult ADHD Self-Report Scale (ASRS-v1.1) [32]. The ASRS-v1.1 is a self-assessment form consisting of 18 questions corresponding to the 18 criteria for ADHD according to the Diagnostic and Statistical Manual of Mental Disorders, Text Revision, 4th edition (DSM-IV-TR). Part A consists of six questions that predict ADHD while part B consists of twelve questions about other symptoms. The ASRS-v1.1 has shown good reliability and validity [32].The Clinical Global Impression-Severity scale (CGI-S). The CGI-S is used for clinical assessment of the severity of symptoms [35]. The CGI–S scale reflects the patient’s total psychiatric impairment. It provides an overall clinician-determined summary measure that takes into account all available information, including knowledge of the person’s history, psychosocial circumstances, symptoms, and behaviour, and the impact of the symptoms on the person’s ability to function.The Clinical Global Impression-Improvement scale (CGI-I) [35]. This is a clinician-rated instrument which provides self-rated global measures of improvement and treatment satisfaction on a 7-point scale, from 1 = very much better to 7 = very much worse [36].

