### Analysis

#### Analysis of quantitative data

Descriptive analysis will be performed and the results will be reported using means ± standard deviations and ranges for continuous variables and numbers and percentages for categorical variables. Data will be analysed with a modified intention-to-treat (ITT) method and all patients involved in at least one data collection will be included in the analysis. Missing values will be imputed with multiple imputation method. Per-protocol (PP) analysis will also be performed where relevant. Analysis of variance (ANOVA) will be performed to compare means of the groups. The differences in baseline characteristics and post-intervention changes between the groups will be tested using *t*-test, Mann-Whitney U test, or Chi-squared test, whichever is appropriate. All analyses will be performed in the statistical software SPSS version 25.0 (IBM Corp., Armonk, NY, US).

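### The protocol contradicts itself on what is primary: one powered scale, three listed scales, a depression scale in the primary block of Table 3, and no primary time point or contrast

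*Protocol article*

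**What the plan says.** - **Sample size estimation:** "The power calculation is based on the primary outcome, ADHD symptom reduction assessed using" ASRS-v1.1. One scale, alpha 0.05, power 0.8, and one difference between intervention and control, although there are two intervention arms.
- **Abstract, Methods:** the primary outcome is measured with "Adult ADHD Self-Report Scale (ASRS-v1.1), Clinical Global Impression-Severity scale (CGI-S) and CGI-Improvement scale (CGI-I". On timing: "The effect will be measured within 1 week after the end of the intervention and 6 and 12 months later".
- **Primary outcome measures:** ASRS-v1.1, CGI-S and CGI-I are described one after another with equal standing. For example: "The Clinical Global Impression-Severity scale (CGI-S). The CGI-S is used for clinical assessment of the severity of symptoms". There is no ranking, no composite, and no rule on whether one or all must succeed.
- **Table 3:** the block headed "Primary outcome measures (ADHD symptoms" has four rows. The fourth scale is MADRS-S, which the text otherwise uses only as an exclusion threshold: "Ongoing depression (Montgomery-Asberg Depression Rating Scale, Self-Assessment (MADRS-S) score > 21".
- **Analysis of quantitative data:** an ANOVA compares group means. In addition, "post-intervention changes between the groups will be tested using" a t-test, Mann-Whitney or Chi-squared test. No outcome, time point or contrast is attached to either.
- **Data collection** counts the 6- and 12-month assessments from the start of the intervention, whereas the abstract's wording counts from its end.

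**The concern.** Readers of the sample size section, the outcome section and Table 3 would name different primary analyses. An analysis plan can add detail to a protocol, but it cannot make one, three and four primary measures agree.

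The three scales are not interchangeable. ASRS-v1.1 is a self-report. CGI-S is a clinician's judgement of overall psychiatric impairment. CGI-I rates improvement. They can disagree, and nothing says which result decides the trial. The alpha and power quoted for ASRS-v1.1 then do not carry over to the claim that the trial worked.

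**Working it through.** **1. The plan's own figure.** Inputs from the sample size section: difference 15%, SD 10.63%, alpha 0.05 (two-sided assumed), power 0.8, drop-out 25%.

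- The drop-out step reproduces: 90 / (1 − 0.25) = 120.
- The 90 does not follow from the inputs. d = 15 / 10.63 = 1.41 needs about 9 per arm (t-test), so 27 in three arms and 27 / 0.75 = 36 randomised. This is a separate matter. It is used here only to judge what the fix costs.

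**2. Counting the candidate tests.**

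- One time point: 3 scales × 2 active-versus-TAU contrasts = 6 tests, or 3 ANOVAs.
- Three time points: 18 tests, or 9 ANOVAs.
- Upper guide if the tests were independent, 1 − (1 − 0.05)^k: k = 3 gives 0.143, k = 6 gives 0.265, k = 9 gives 0.370, k = 18 gives 0.603.

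**3. Allowing for correlation.** The documents give no correlations, so these are assumptions: 0.3, 0.5 and 0.7 between scales, and 0.6 between time points. I simulated no effect with 30 per arm, normal data, a shared control and each test at two-sided 0.05 (20,000 runs per setting, Monte Carlo standard error at most about 0.35 percentage points). The table gives the chance of at least one false positive if any positive result counts.

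| Readings counted as primary | ANOVA gates the two contrasts | ANOVA alone | Ungated contrasts |
|---|---|---|---|
| 1 scale, 12 weeks | 4% | 5% | 9% |
| 3 scales, 12 weeks | 9–12% | 11–14% | 19–24% |
| 3 scales, three time points | 22–26% | 26–30% | 41–48% |

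**4. The opposite rule.** If all three scales had to succeed, alpha would not exceed 0.05 per contrast. If each scale had power 0.8, joint power per contrast would lie between 0.8³ = 0.51 (independent scales) and 0.80 (perfectly correlated scales).

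**5. Power after the fix.** Two contrasts on one endpoint, with the strictest Holm step at 0.05 / 2 = 0.025 and 30 per arm:

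- On the stated inputs (d = 1.41), power stays above 0.99.
- If the 90 instead reflects the smallest difference detectable with 30 per arm at 0.05 (about 0.74 SD, or 0.74 × 10.63 ≈ 7.8%), power at 0.025 falls to about 0.71 by t-test. The normal approximation gives 0.736 × √15 − 2.241 = 0.61, hence about 0.73.

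**The case against.** Four objections deserve an answer.

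- **The error rate depends on a rule the protocol never states.** This stands. Inflation occurs only if any positive result counts. A reader might infer that the trial's type I error *is* 40% or more. The documents do not support that: they name no such rule, they do not make the follow-ups co-equal primaries, and they state a three-group ANOVA, which gives much lower figures than ungated pairwise tests. Equally, nothing says that the ANOVA acts as a gate. The supportable statement is that error control is not fixed by what is written.
- **The text leans towards 12 weeks.** It does. Table 3 labels that column as the end of the intervention and the later ones as follow-up. But the abstract lists all three times together as when the effect is measured, and none is named primary.
- **MADRS-S in Table 3 is probably a misplaced row.** Probably so, because the outcome section does not describe it. A reader might infer a fourth primary outcome, but the evidence for that is weak. The row still needs correcting, and no figure above depends on it.
- **Multiplicity rules belong in an analysis plan.** Often true, and their absence alone would be no finding. The contradiction between sections is in the protocol itself.

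A reader might also infer that the later comparisons are contaminated by controls taking up training. The Discussion says otherwise: controls who start it are removed from long-term follow-up. The issue there is selection after randomization. Its size is unknown, and uptake was low in the pilot.

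**Conclusion.** The point holds as an internal contradiction about what decides the trial. The sample size section has one primary scale, the abstract and outcome section have three without ranking, and Table 3 has an extra row. No primary time point or contrast is fixed. The quoted 0.05 and 80% therefore do not apply to the primary decision as written.

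The size is conditional. If any positive scale at 12 weeks counted, the false-positive chance would be about 9–14% with the stated ANOVA and 19–24% with ungated contrasts. Counting the 6- and 12-month readings as well would raise it to about 22–30% and 41–48%. These figures rest on assumed correlations, 30 per arm and two-sided tests. Requiring all scales to succeed, or one ANOVA on ASRS-v1.1 at 12 weeks, would leave alpha intact. The protocol commits to none of these.

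**What to change.** - Name ASRS-v1.1 total score at 12 weeks as the single primary endpoint, in line with the sample size section.
- Test MEP versus TAU and MEP-C versus TAU within an overall alpha of 0.05. Holm is one option. Using the stated ANOVA as a gate is another, which suffices for three arms on a single endpoint.
- Make CGI-S, CGI-I and all 6- and 12-month results secondary. The exclusion of controls who start training is a further reason not to let later readings compete for primary status.
- Move MADRS-S out of the primary block of Table 3, and state one origin for the follow-up times.
- Record the change, with its date, before analysts see results by group. The protocol already plans blinded analysts, but data collection began in March 2021, so this is a change to an ongoing trial and should be reported as such.

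**Cost.** On the stated 15% and 10.63%, no extra patients are needed. If the 90 really rests on a difference near 0.74 SD, a 0.025 step lowers power to roughly 0.7, and the power statement should say so.

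The real downside is that the clinician ratings lose primary status and the sole primary is a self-report by participants who know their allocation, which the Discussion itself names as a source of expectation bias. CGI results should therefore be reported beside it as key secondary outcomes.

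If the sponsor prefers to keep the CGI scales primary, Holm must cover all six scale-by-contrast tests (first step 0.05 / 6 = 0.0083), and power must be restated for each scale.

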**Discussion:**

Data collection began in March 2021. The final 12-month follow-up is anticipated to be completed by autumn 2024.

**Trial registration:**

ClinicalTrials.gov (Identifier: NCT05049239). Registered on 20 September 2021 (last verified: May 2021).

## Background

The prevalence of attention deficit hyperactivity disorder (ADHD) in adults is estimated to be 2.5–5% [1, 2]. The core symptoms of ADHD are inattention, impulsivity and hyperactivity [3]. People with ADHD may also have impaired executive function, which among other things includes difficulty in time management and structuring of everyday life. Adults with ADHD have been shown to have difficulty finding and maintaining gainful employment and experience a high degree of stress in managing everyday life [4], leading to fatigue and poor sleep quality and quantity [5–7]. Brain imaging studies have shown structural and functional abnormalities in key brain areas including the basal ganglia and the cerebellum, which are more accentuated in children and adolescents than in adults. Some of these functional abnormalities may be normalized by pharmacological treatment with stimulant medication [8, 9].

People with ADHD have a high prevalence of comorbidity with other mental disorders such as anxiety disorders and depression [10]. A major risk factor for secondary diseases is also the patients’ sedentary lifestyle, with little movement and exercise [5–7, 10, 11]. Moreover, people with ADHD have substantial problems with emotion regulation, which can negatively impact interpersonal relationships both at home and at work [4].

Currently, the first-line treatment option in adult ADHD is pharmacological treatment with central stimulants (CSs) although guidelines recommend multimodal treatment [12]. The response rate to pharmacological treatment is high; however, up to 30% of patients fail to respond to CS medication [13]. There are a number of non-pharmacological treatment options that are used in the clinical setting, but the evidence for these is often lacking [10, 11], and there is a need for well-designed randomized controlled trials (RCTs) to evaluate them.

Physical activity improves mood and sleep, boosts energy, supports healthy ageing and lowers the risk for all-cause mortality by reducing, among other things, risks for cardiovascular disease and type-2 diabetes [14]. In children with ADHD, physical exercise has been shown to improve problems of inattention, hyperactivity and impulsivity [15–21], but in adults with ADHD there is still a lack of knowledge. In general, moderate to vigorous exercising for at least 150 min a week greatly reduces the risk of cardiovascular disease, diabetes and premature death and has major effects on the mental state and illnesses such as depression and anxiety [15, 16, 22]. Whether such activity levels can also reduce ADHD symptoms in adults remains to be investigated.

It is also not known whether, and how, physical exercise can affect the brain’s structure and function in adults with ADHD [18]. Physical exercise is a way to gain increased experience of the body and can strengthen a person’s confidence in their own physical ability [7, 23]. This is related to body awareness, which is the experience of “living in the body” and forms the basis for self-confidence and the ability to take care of oneself and one’s needs. Research has shown that an increased experience of the body provides increased wellbeing [24]. However, whether physical exercise improves body awareness in adults with ADHD remains to be investigated. To our knowledge there are no studies that examine how body awareness is affected by physical exercise in adults with ADHD or whether there is a relationship between emotion regulation, self-efficacy and body awareness in adults with ADHD. There is moderately strong scientific evidence that physical exercise can affect sleep quality and fatigue, regardless of etiology, and that energy levels increase in individuals who are physically active [16, 25]. However, there are no studies examining whether physical exercise improves sleep quality and perceived fatigue in adults with ADHD.

In a pilot study ahead of this planned RCT, an intervention including a mixed exercise programme (MEP) was evaluated in 14 adult participants with ADHD [26]. Nine participants were randomized to the intervention group, and five to the treatment as usual (TAU) control group. Three participants dropped out shortly after inclusion, before receiving any intervention; the remaining eleven (approx. 80%) conducted the intervention/treatment according to protocol. Overall, participants were satisfied and reported no major difficulties in following the intervention. The results were highly consistent with trends in post-intervention changes for almost all outcome variables.

One challenge that was seen in the pilot study was that some participants had difficulty in organizing and making time for the 12-week intervention. To plan, accomplish and evaluate activities, executive functioning is fundamental, which is also the case when it comes to performing physical activities. There are few intervention studies that have evaluated the effect of cognitive interventions for adults with ADHD; however, the few studies available show that cognitive skills training improves the everyday functioning of adults with ADHD [27–30]. These intervention studies regarding structured cognitive interventions including skills training for adults with ADHD report that implementation of person-centred strategies for planning daily activities improved the individuals’ performance and increased their self-esteem and confidence in their own ability [27, 29].

To conclude, there are currently several knowledge gaps in the treatment of adult ADHD. The evidence for physical exercise, or physical exercise in combination with a person-centred, structured cognitive intervention, as a treatment for ADHD symptoms in adults is deficient. There is therefore a great need for further studies to investigate whether physical exercise with or without cognitive intervention has the same effect on ADHD symptoms in adults as in children and adolescents [4, 17, 18, 20].

### Rationale

Regular physical activity has a positive effect on ADHD core symptoms in children and adolescents, but corresponding evidence regarding this effect on symptoms in adults is lacking and there is a great need to study this [2, 5, 14]. People with ADHD face challenges in their everyday life, challenges of inattention, impulsivity and hyperactivity, but they also exercise less and have a sedentary lifestyle. People with ADHD also struggle with the structure of everyday life and there are studies that show that structured cognitive skills training improves the everyday functioning of adults with ADHD. However, it has not been studied whether such training can contribute to increased physical activity or to maintaining routines for this. Today, the guidelines recommend multimodal treatment for people with ADHD, in other words, a combination of pharmacological and non-pharmacological interventions [12]. If our study can prove that the START intervention (START = *Stöd i Aktivitet, Rörelse och Träning* [Support in activity, movement and exercise]) can improve the core symptoms and quality of life (QoL) for adult patients with ADHD, it could be a welcome addition to the available treatment options. The goal is to develop a multimodal, non-pharmacological intervention of physical exercise with or without cognitive skills training as treatment for ADHD and to test this in an RCT.

### Aim

The main aim is to implement the 12-week START intervention consisting of a structured MEP with or without cognitive skills training in adults with ADHD, and to study whether it has an effect on core symptoms of ADHD as well as physical, cognitive, mental and everyday functioning, compared with treatment as usual (TAU). TAU consists of pharmacological or non-pharmacological treatment without physical exercise. A further aim is to describe the participants’ experiences of the intervention and its possible benefits, and to evaluate the cost-effectiveness of START compared with TAU.

## Method

### Design

This study is a planned prospective RCT in three parallel groups of adults diagnosed with ADHD, following the SPIRIT guidelines [31].

Randomization into three groups will be as follows:

Physiotherapist-led structured physical exercise group (n = 40);Physiotherapist-led structured physical exercise group with occupational therapist-led, person-centred cognitive skills training (n = 40);Control group receiving TAU (n = 40). For a flow chart of the trial design, see Fig. 1.

